### Drug storage and stability

Sintilimab Injection: must be stored at 2°C to 8°C (36°F to 46°F) and protected from light, shock and freezing. The unopened vials can be stored at room temperature (up to 25°C, 77°F) and room light for up to 48 hours. The administration of Sintilimab infusion must be completed within 24 hours of preparation. If not used immediately, the infusion solution may be stored under refrigeration conditions (2°C to 8°C, 36°F to 46°F) for up to 24 hours, and a maximum of 8 hours of the total 24 hours can be at room temperature (up to 25°C, 77°F) and room light. The maximum of 8 hours under room temperature and room light conditions includes the product administration period.

The investigator, or his/her authorized representative (eg, pharmacist), will ensure that all study drug is stored in a secure area with controlled access that meets storage conditions and is stored in compliance with applicable regulatory requirements.

### Dosing Regimen

Sintilimab monotherapy after radiotherapy (3 cycles)

**The specific dose and mode of administration are as follows:**

Sintilimab: 200 mg, every 3 weeks, with 21 days as a cycle. This product is for intravenous injection only. Intravenous infusion over 30 minutes. The infusion tube used in the infusion must be equipped with a sterile, pyrogen-free, low-protein-binding infusion tube filter (pore size 0.2-1.2 μm). This product should not be administered by intravenous bolus or single rapid intravenous injection. This product can be directly infused with 10mg/ml solution, or diluted with sodium chloride solution for injection (9mg/ml, 0.9%) or glucose solution for injection (50mg/ml, 5%), the concentration can be as low as 1mg/ml.

The study drug is administered until the protocol-specified treatment termination criteria occur.

Imaging assessment is performed for the subjects within 1 weeks of the last dose of Sintilimab therapy; surgery is performed for operable subjects 2 weeks after the last dose.

### Dose Adjustments

Every effort should be made to give each subject access to the study drug according to the protocol. If study treatment interruption and/or dose adjustment are required due to adverse drug reactions, toxicity should be classified according to National Cancer Institute (NCI) Common Toxicity Criteria (CTC) Version 5.0, and the reasons for interruption/adjustment, actions taken and results should be recorded.

General principles for dose modification:

- Dose delays/modifications due to the toxicity of chemotherapy agents or Sintilimab may not affect the planned use of other study agents.
- The investigator may delay the full combination treatment (up to 14 days) to maintain synchronization of study treatments, as appropriate.
- Sintilimab should be administered no less than 12 days apart;

#### Dose modifications for nivolumab

For serious adverse reactions with Sintilimab, dosing may be interrupted or permanently discontinued based on the safety and tolerability of individual patient. Dose escalation or reduction is not recommended.

Immune-related adverse reactions: See the study procedures in Guidelines for the Management of Toxicity Associated with CSCO Immune Checkpoint Inhibitors (2021.V1) for specific management principles

## Screening Period

Tumor assessment, including tumor imaging assessment (CT/MRI/PET), endoscopy and pathological assessment, should be performed within 21 days of enrollment. Imaging examinations include chest CT, enhanced CT scan of abdomen and pelvis (CT scan slice thickness ≤ 5 mm). If allergic to enhanced CT contrast agent, chest CT plain scan + abdominal and pelvic MRI scan can be performed; if brain metastasis is suspected, brain enhanced MRI or enhanced CT should also be performed to rule out brain metastasis. Bone scan should be performed when bone metastasis is clinically suspected.

The following information will be collected within 14 days of enrollment:

- Blood routine: WBC, neutrophils, lymphocytes, RBC, hemoglobin and platelets;
- Blood biochemistry: including total bilirubin, direct bilirubin, ALT, AST, AKP, γ-GT, total protein, albumin, urea nitrogen/urea nitrogen, creatinine, endogenous creatinine clearance rate, uric acid, fasting blood glucose, triglyceride, cholesterol, potassium, sodium, chloride, calcium and phosphorus;
- Serum amylase: lipase test should be performed in case of abnormal serum amylase with clinical significance;
- Urinalysis: including urine protein, urine glucose, urine occult blood, urine red blood cells, white blood cells. If 2 consecutive semiquantitative assays show protein 2+, 24-hour urinary protein quantification test is performed, and if semiquantitative assay shows protein > 2+, 24-hour urinary protein quantification test is performed;
- Stool occult blood test: If stool occult blood is positive, reexamination should be performed. After reexamination, stool occult blood is still positive. Combined with clinical judgment, gastroscopy should be performed when necessary
- Coagulation function: including INR, APTT, PT and FIB;
- For subjects of childbearing potential, serum human chorionic gonadotropin (HCG) test is performed within 72 hours before enrollment;
- Cardiac enzymes: creatine kinase MB isoenzyme (CK-MB), troponin I (cTnI), lactate dehydrogenase;
- Vital signs (performed after sitting quietly for 5 minutes): including body temperature, blood pressure, pulse and respiratory rate;
- A complete physical examination is performed: general condition, head and face, skin, lymph nodes, eyes, ears, nose and throat, oral cavity, respiratory system, cardiovascular system, abdomen, genito-urinary system, musculoskeletal system, nervous system, and mental status;
- Height and weight measurement;
- ECOG scoring;
- 12-lead ECG (performed after sitting quietly for at least 5 minutes): heart rate, PR interval and QTc interval;
- Echocardiogram, including LVEF assessment;
- Blood pressure monitoring;
- Collection of concomitant medications/treatments;
- Collection of AEs;
- Verification of inclusion and exclusion criteria.
- Subjects may be enrolled if all inclusion criteria are met and none of the exclusion criteria are met.

## Treatment period and end of treatment

Study medication is detailed in 5.1.2 Regimen.

Relevant physical examinations and laboratory tests are performed during treatment to collect AEs and concomitant medication information.

During the treatment period, imaging examinations should be performed under the same conditions as the baseline examination (slice thickness of the scan, use of contrast agent, etc.), within 1 weeks after radiotherapy; within 1 weeks after the frist dose of PD-1 monoclonal antibody in Cycle 3; imaging assessment should be performed at the end of treatment; if treatment is discontinued due to reasons other than radiographic progression during the treatment period, imaging examination should be performed at the end of treatment, unless imaging examination has been performed within 28 days.

The following tests should be completed before administration on Day 1 of each treatment cycle, at the preoperative assessment and at the end of treatment. If the scheduled visit tests before the first dose have been performed during the screening period and within 3 days before the first dose, they may not be repeated before administration in Cycle 1:

- Blood routine: WBC, neutrophils, lymphocytes, RBC, hemoglobin and platelets;
- Blood biochemistry: including total bilirubin, direct bilirubin, ALT, AST, AKP, γ-GT, total protein, albumin, urea nitrogen/urea nitrogen, creatinine, endogenous creatinine clearance rate, uric acid, fasting blood glucose, triglyceride, cholesterol, potassium, sodium, chloride, calcium and phosphorus;
- Urinalysis: including urine protein, urine glucose, urine occult blood, urine red blood cells, white blood cells. If 2 consecutive semiquantitative assays show protein 2+, 24-hour urinary protein quantification test is performed, and if semiquantitative assay shows protein > 2+, 24-hour urinary protein quantification test is performed;
- Blood occult blood test: performed if necessary;
- Coagulation function: including INR, APTT, PT and FIB;
- For subjects of childbearing potential, pregnancy tests are performed as necessary during the treatment period.
- Cardiac enzymes: performed as necessary, including creatine kinase MB isoenzyme (CK-MB), troponin I (cTnI), lactate dehydrogenase;
- Vital signs (performed after sitting quietly for 5 minutes): including body temperature, blood pressure, pulse and respiratory rate;
- Physical examination: Targeted physical examination is performed as clinically indicated;
- Height and weight measurement;
- ECOG score;
- 12-lead ECG (performed after sitting quietly for at least 5 minutes): performed as necessary, including heart rate, PR interval and QTc interval;
- Echocardiogram: performed as necessary, including assessment of LVEF;
- Blood pressure monitoring

Subjects receiving nivolumab will undergo the following tests before dosing on Day 1 of each cycle and at the end of treatment in addition to the above tests:

- Serum amylase: lipase test should be performed in case of abnormal serum amylase with clinical significance;
- Thyroid function test (C1D1 not required);

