# Study medication

## Overview of investigational product

In the study, study drugs are defined as Sintilimab.

|  | Sintilimab |
| --- | --- |
| Manufacturer | Innovent, China |
| Dose Form | Injection fluid |
| Strength | 100 mg |
| Route of Administration | Intravenous |

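### The on-treatment amylase and thyroid tests are required only of patients on nivolumab, a drug nobody in this trial receives

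*Protocol*

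**What the plan says.** The Protocol names one study drug: "In the study, study drugs are defined as Sintilimab". The dosing section gives it alone after radiotherapy, for three cycles: "Sintilimab: 200 mg, every 3 weeks, with 21 days as a cycle". The Protocol Summary and Overall Design also give sintilimab as the only PD-1 antibody.

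Under Treatment period and end of treatment there are two test lists. The first is unconditional: "The following tests should be completed before administration on Day 1 of each treatment cycle", and also at the preoperative assessment and at end of treatment. The second adds serum amylase (lipase if amylase is abnormal) and thyroid function (waived on Day 1 of cycle 1), but it opens with a condition: "Subjects receiving nivolumab will undergo the following tests before dosing on Day 1 of each cycle and at the end of treatment".

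The same drug name heads a subsection under Dose Adjustments, "Dose modifications for nivolumab", yet the text beneath it concerns the actual study drug: "For serious adverse reactions with Sintilimab, dosing may be interrupted or permanently discontinued".

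**The concern.** The condition on the second test list is met by no one in the trial, so on its wording the list applies to nobody. A wrong drug name in a background paragraph would be harmless. Here it decides who is tested.

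At stake is the detection of immune-related events that show only in the laboratory. The immune-related adverse event rate is a secondary endpoint, counted from the start of PD-1 inhibition to day 30 after surgery. The adverse event definition includes laboratory abnormalities that are clinically significant. A thyroid or pancreatic abnormality without symptoms can enter that rate only if somebody measures it. If some staff apply the list and others skip it, the rate depends in part on how the sentence was read, and a single-arm trial has no control group in which the same under-detection would occur.

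**Working it through.** The Protocol states no figure to reproduce. The check is a reading of each place where the drug or the tests appear, followed by a count.

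**Who receives nivolumab?** The name appears in three places:
- in the background, as the treatment in another study;
- in the heading on dose modifications, above text about sintilimab;
- in the condition on the second test list.

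No section gives it to a trial patient, so the number meeting the condition is 0.

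**Does another section require the tests?**

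| Section | Amylase | Thyroid function |
|---|---|---|
| Screening Period | Yes: "Serum amylase: lipase test should be performed in case of abnormal serum amylase with clinical significance" | Not listed |
| Treatment period, unconditional list | Not listed | Not listed |
| Treatment period, nivolumab list | Each Day 1 and end of treatment | Each Day 1 except cycle 1, and end of treatment |
| Follow-up Period | Not listed | Not listed |

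The toxicity guideline cited under Dose Adjustments is invoked for managing immune-related reactions. The Protocol takes no test schedule from it.

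**Can the screening amylase stand in?** Per the Protocol Summary, chemoradiotherapy lasts 5 weeks and sintilimab starts on day 15 after it ends. The gap from the start of radiotherapy to the first dose is 5 × 7 + 15 = 50 days, and 50 / 7 ≈ 7 weeks, plus any interval between screening and radiotherapy. Screening amylase is a baseline value and says nothing about events on treatment.

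**How many tests depend on the name?** For a patient who completes three cycles:
- Thyroid: 3 Day 1 visits − 1 (cycle 1 waived) + 1 at end of treatment = 3.
- Amylase: 3 Day 1 visits + 1 at end of treatment = 4.
- Total: 3 + 4 = 7 under the intended reading, 0 under the literal one.

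The Protocol gives two enrolment targets: 30 in the Protocol Summary, 46 in Overall Design and Sample Size.
- 7 × 30 = 210 tests.
- 7 × 46 = 322 tests.

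Both totals are upper bounds, because they assume that every patient completes three cycles. The Protocol Summary gives sintilimab weekly for 3 weeks and the dosing section every 3 weeks. Both mean three administrations, so the count does not change if each administration is taken as one cycle.

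**The case against.** The strongest reply is that nobody would read the sentence literally. The trial has one arm and one study drug, the section opens by referring back to the sintilimab regimen, and the only cycles dosed are sintilimab cycles. The heading on dose modifications shows that the name is a leftover. The tests are listed and timed, down to a waiver for cycle 1, so the intent is plain.

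Much of this stands: sintilimab is the likely intended meaning. It does not settle the matter, because a second reading is also available. The sentence is worded as applying to a subset of patients, and the document carries other text that plainly does not belong, such as gastric cancer patients in Overall Design and gastric distension under RECIST evaluation. A reader used to skipping such text could skip this paragraph too. The two readings give opposite schedules.

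A second objection is that the effect on the endpoint is limited. A laboratory value counts as an adverse event only if it is clinically significant, and it enters the immune-related rate only if attributed to PD-1 inhibition. Many symptom-free changes would therefore not count even with full testing. This also stands, and it narrows the effect. It does not remove it, since an abnormality that was never measured cannot be judged significant or attributed.

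A third objection is that the test counts measure neither bias nor missed events. That is correct. They show only how much of the schedule depends on one word.

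Finally, correcting the name leaves no baseline thyroid value, because screening lists no thyroid test and cycle 1 Day 1 is waived. This is true, but it is a separate gap and does not weaken the case for the correction.

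**Conclusion.** The concern holds. As written, the Protocol requires none of the 7 on-treatment amylase and thyroid tests for a patient who completes three cycles, and no other section fills the gap.

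The consequence is bounded. Liver, kidney, glucose and blood count tests remain unconditional at each cycle, symptomatic events are still collected as adverse events, and the primary endpoint is untouched. The Protocol does not show that any test was omitted. The effect on the immune-related adverse event rate cannot be estimated, because the document gives no event frequencies; if there is one, it is towards understatement. The conclusion rests on the literal wording of the condition, and the totals of 210 and 322 rest on every patient completing three cycles.

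The sentence should be corrected because it governs a safety schedule and supports a secondary endpoint. The heading on its own would be a clerical matter.

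**What to change.** Replace nivolumab with sintilimab in the sentence that introduces the amylase and thyroid tests under Treatment period and end of treatment, and in the heading on dose modifications under Dose Adjustments. The listed tests then apply to every patient given the study drug.

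The cost is a one-word amendment in two places. The tests and their timing are already written, so no procedure or visit is added. In the same amendment the sponsor could consider a baseline thyroid test before the first sintilimab dose. That would be a new test and is not needed for this correction.

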## Inclusion Criteria

Patients must meet all of the following inclusion criteria to be enrolled in the study:

1. Patients voluntarily participate in the study and sign the informed consent form;
2. Age ≥ 18 years and ≤ 80 years;
3. Previously untreated and confirmed by biopsy as rectal adenocarcinoma;
4. MRI shows no distant metastasis, stage II/III (except T4b)
5. The lower edge of the tumor must be within 10 cm of the anal margin;
6. Willing and able to comply with the research protocol;
7. Agree to use blood and tissue samples for research;
8. No history of anti-tumor treatment (such as radiotherapy, chemotherapy, immunotherapy, biology, herbal medicine, etc.);
9. ECOG score 0-2;
10. No immune system diseases (such as systemic lupus erythematosus, rheumatoid arthritis, systemic vasculitis, scleroderma, pemphigus, dermatomyositis, mixed connective tissue disease, autoimmune hemolytic anemia, hyperthyroidism/hypothyroidism, ulcerative colitis, autoimmune hemolytic anemia, HIV infection, etc.);
11. No significant functional impairment of major organs (such as heart, lungs, liver, kidneys, etc.);
12. No jaundice or gastrointestinal obstruction; No acute/chronic infection;
13. No obvious abnormalities in blood routine and biochemical tests: neutrophils≥1.5×109/L, hemoglobin≥80g/L, platelets≥100×109/L, total bilirubin≤1.5×ULN, ALT, AST≤2.5×ULN;
14. No social or mental disorders;
15. For women of childbearing age, the serological pregnancy test result needs to be negative, and effective contraception measures need to be taken within 60 days;

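### No thyroid test is scheduled before the first sintilimab dose: the Cycle 1 Day 1 test is waived and screening contains none

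*Protocol*

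**What the plan says.** Thyroid function is mentioned in two contexts in the Protocol.

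- **Eligibility.** The Inclusion Criteria (and the matching row of the Protocol Summary) require that the patient has no immune system disease. The examples run through "autoimmune hemolytic anemia, hyperthyroidism/hypothyroidism, ulcerative colitis". This is a diagnosis; no thyroid test or threshold is attached. The laboratory eligibility criterion covers neutrophils, haemoglobin, platelets, bilirubin, ALT and AST only.
- **Treatment period.** Under Treatment period and end of treatment, an additional list opens with "Subjects receiving nivolumab will undergo the following tests before dosing on Day 1 of each cycle and at the end of treatment". It has two items, serum amylase and thyroid function, and the second reads "Thyroid function test (C1D1 not required".

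The Screening Period section itemises its tests under "The following information will be collected within 14 days of enrollment". The list includes "Serum amylase: lipase test should be performed in case of abnormal serum amylase with clinical significance" and ends with "Verification of inclusion and exclusion criteria". It contains no thyroid test. The general Day 1 list in the treatment-period section, introduced by "The following tests should be completed before administration on Day 1 of each treatment cycle", contains none either.

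**The concern.** Waiving a test on the first dosing day is reasonable when screening has just supplied the value. The protocol applies that logic to the general Day 1 tests: they may be omitted in Cycle 1 if done in screening and within 3 days before the first dose. For thyroid function there is no screening value to rely on, so the waiver removes the only pre-dose measurement.

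Two things are at stake. The first is safety: later thyroid results have no pre-dose value to be read against. The second is a secondary endpoint. The immune-related adverse event rate counts events judged to be associated with PD-1 inhibition, from its start to 30 days after surgery. The adverse event definition covers both new conditions and worsening of existing ones, and the causality section asks the investigator to weigh the time sequence. For an abnormality first seen after exposure, with no earlier value, neither judgement has a laboratory basis.

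**Working it through.** **Step 1. The schedule side by side.** Cycles are read as sintilimab cycles, since the Dosing Regimen section defines 21-day cycles for that drug. The word nivolumab in the introductory sentence is read as sintilimab, because no patient in this trial receives nivolumab. Read literally, the sentence would schedule no thyroid test for anyone.

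| Time point | Serum amylase | Thyroid function |
|---|---|---|
| Screening | scheduled | not listed |
| Cycle 1 Day 1 | scheduled | waived |
| Cycle 2 Day 1 | scheduled | scheduled |
| Cycle 3 Day 1 | scheduled | scheduled |
| End of treatment | scheduled | scheduled |

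Scheduled thyroid values before the first sintilimab dose: 0. Amylase, the companion item in the same list, has 2.

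**Step 2. Delay to the first value.** The Dosing Regimen gives 21 days between doses, so the first thyroid result comes 21 days after dose 1. Under Dose Adjustments, "Sintilimab should be administered no less than 12 days apart", so it cannot come earlier than 12 days after. The Protocol Summary and Overall Design instead say weekly dosing. That would make it 7 days, below the 12-day minimum. On any of these readings the first value follows exposure, so the point does not depend on which interval is right.

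**Step 3. Would a screening test alone be enough?** Twenty-five fractions at 5 per week run from day 1 to day 33. The first sintilimab dose, on the 15th day after chemoradiotherapy ends, falls on day 33 + 15 = 48. A screening sample taken no later than day 1 would be at least 48 − 1 = 47 days old, or 47/7 = 6.7 weeks. A sample at Cycle 1 Day 1 is the better baseline.

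**Step 4. Possible effect on the immune-related adverse event rate.** If k patients are misclassified and have no other immune-related event, the rate moves by k/n. It rises if a pre-existing abnormality is attributed to sintilimab and falls if a sintilimab-related one is taken as pre-existing. The protocol gives two enrolment targets: 30 in the Protocol Summary, and 46 in Overall Design and Sample Size. Safety is analysed in patients who received at least one dose of the investigational drug. The last two columns therefore assume, for illustration, that the whole planned 10% drop-out occurs before sintilimab: 30 × 0.9 = 27 and 46 × 0.9 = 41.4, taken as 41.

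| k | n = 30 | n = 46 | n = 27 | n = 41 |
|---|---|---|---|---|
| 0 | 0 | 0 | 0 | 0 |
| 1 | 3.3 | 2.2 | 3.7 | 2.4 |
| 2 | 6.7 | 4.3 | 7.4 | 4.9 |
| 3 | 10.0 | 6.5 | 11.1 | 7.3 |

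Entries are percentage points. The values of k are illustrative; nothing in the protocol allows k to be estimated.

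**The case against.** The strongest counter-argument is that eligibility already handles this. Patients with hyper- or hypothyroidism are not eligible, the criteria must be verified at screening, and a full physical examination and the record of concomitant medication would help to reveal known or treated disease. That leaves only patients with undiagnosed thyroid dysfunction, or with an early sintilimab effect, whose abnormality is present at Cycle 2 Day 1 and clinically significant enough to count as an adverse event. Causality can still be graded, and the five-level scale includes an indeterminable category. An abnormality that appears after a normal Cycle 2 Day 1 result is not affected. An investigator may also order a thyroid test unprompted.

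Most of this stands. It limits the problem to a small group that may be empty, and it means attribution is weakened rather than impossible. The k/n figures show sensitivity per patient and are not evidence that any patient will be misclassified.

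It does not remove the gap. A history-based exclusion does not detect undiagnosed dysfunction, and an unscheduled test cannot be relied on when the text expressly waives it. Nor is this a matter for a statistical analysis plan, because no analysis can recover a sample that was never drawn.

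**Conclusion.** The concern holds. Followed exactly, the protocol yields no scheduled thyroid laboratory value before the first sintilimab dose. The consequence is loss of the pre-dose safety reference and weaker attribution for abnormalities already present at Cycle 2 Day 1. The possible shift in the immune-related adverse event rate is 3.3 points per affected patient at 30 enrolled and 2.2 at 46, and slightly more if the Safety Set is smaller. The number affected is unknown and may be zero.

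The conclusion rests on reading nivolumab as sintilimab in the sentence that introduces the test. The change should be made because it is cheap and the missing value cannot be recovered later; the case does not depend on a large expected effect.

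**What to change.** Under Treatment period and end of treatment, delete the Cycle 1 Day 1 exception and require thyroid function before the first sintilimab dose, in the blood draw that the general Day 1 list already schedules. In the sentence that introduces the list, replace nivolumab with sintilimab. Adding the test at screening as well is optional: it would give the thyroid eligibility criterion a laboratory check but would not replace the pre-dose value.

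For patients already treated without a pre-dose value, report thyroid events first seen at Cycle 2 Day 1 separately as having no baseline, and give the immune-related adverse event rate with and without them.

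The cost is one thyroid assay per patient (30 or 46 in total, depending on which enrolment target applies) and a short amendment to the wording. No extra visit is needed.
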